## Abstract

**Background:**

Colorectal cancer (CRC) ranks as the third most common cancer globally, with significant postoperative recurrence and metastasis rates. The heterogeneity of CRC presents challenges in the selection of adjuvant chemotherapy regimens, highlighting the need for personalized treatment strategies. The development of in vitro models for drug sensitivity testing, including a novel patient-derived tumor-like cell cluster (PTC) model, offers a potential solution for predicting drug efficacy and guiding treatment.

**Methods and design:**

This multicenter randomized controlled trial (RCT) aims to evaluate the consistency between the in vitro PTC drug sensitivity test results with whole exome sequencing and the clinical prognosis of CRC patients. The study will involve 200 patients who will be randomly assigned to receive either PTC-guided adjuvant chemotherapy or traditional chemotherapy. The primary endpoint is the 3-year disease-free survival rate (3yDFS), with secondary endpoints including the consistency between test results and clinical outcomes and the prognostic value of gene mutations and other biomarkers.

**Discussion:**

This study represents a significant step toward precision medicine in CRC treatment by integrating PTC technology with whole-exome sequencing. These findings could provide valuable insights into personalized treatment approaches, potentially improving the clinical outcomes of patients with CRC.

**Trial registration:**

ClinicalTrials.gov: NCT05424692. Registered on June 21, 2022.

## 1 Background

Colorectal cancer (CRC) is a common gastrointestinal malignancy that seriously endangers human health. According to cancer statistics 2023 [1], CRC has become the third most common cancer in terms of both incidence and mortality rates. Approximately 25–30% of stage II CRC patients experience recurrence and metastasis within 5 years after surgery, whereas approximately 50–60% of stage III CRC patients experience recurrence and metastasis within 5 years after surgery [2,3]. In addition, 45–50% of patients with stage II-III disease develop liver metastases within two years after primary resection [4,5]. As the main adjuvant treatment for CRC surgery, multiple international clinical studies have shown that surgery combined with adjuvant chemotherapy can achieve a total 5-year survival rate of 60–70% and a total 5-year disease-free survival rate of 55–65% for high-risk stage II and stage III patients [6,7].

However, CRC is a malignant tumor with significant heterogeneity [8,9], and there are significant individual differences in drug sensitivity among patients. Even patients with the same pathological type and clinical stage who receive the same treatment plan have different prognoses and outcomes [10]. The selection of adjuvant chemotherapy regimens for different subgroups of patients remains controversial. Therefore, constructing a model that can accurately predict drug efficacy and guide personalized treatment for patients is one of the strategies for achieving precision treatment of CRC. Scientists have been dedicated to developing in vitro models for drug sensitivity testing over the past century, including cell lines, primary tumor cells [11], patient-derived organoids (PDOs) [12], and patient-derived tumor xenograft (PDX) mice [13]. However, owing to issues such as standardization, accuracy, and cycle, these methods have certain limitations in clinical application and struggle to achieve true clinical translation.

In 2020, [name] team developed a novel in vitro model called patient-derived tumor-like cell clusters (PTCs) [14]. Three-dimensional microspheres are formed by the self-assembly of tumor cells and tumor stromal cells from patient samples after cutting, digestion, and proliferation. The resulting PTCs include various cells derived from tumor tissue, such as tumor epithelial cells, tumor stem cells, fibroblasts, and immune cells, which can simulate the tumor microenvironment to a certain extent. The PTC model is highly similar to the original tumor tissue in terms of morphology, pathological characteristics, genetic background, and other dimensions [15]. For gastrointestinal tumors, the consistency between PTC drug sensitivity test results and clinical efficacy reached 96.6% [14]. Therefore, the high accuracy of PTC drug sensitivity testing technology has been preliminarily confirmed.

On the basis of the above background, this study aims to conduct a multicenter randomized controlled trial to compare the consistency between the in vitro PTC drug sensitivity test results and the clinical prognosis of CRC patients. The goal is to explore the decision-making value and guiding significance of this technology for assisting in precision treatment of CRC. This study will provide a valuable reference for achieving individualized and precise treatment of CRC patients and offer real-world data support for the clinical application of PTC drug sensitivity testing technology.

## 2 Methods and design

### 2.1 Study overview

This multicenter randomized controlled trial (RCT) will be conducted at 9 tertiary hospitals: Peking Union Medical College Hospital, Tianjin People’s Hospital, Chinese PLA General Hospital, Beijing Chaoyang Hospital Affiliated with Capital Medical University, Huazhong University of Science and Technology Tongji Medical College Affiliated Union Hospital, Dalian Medical University Affiliated First Hospital, The Second Affiliated Hospital of Harbin Medical University, Cancer Hospital of Xiangya Medical College Central South University, and Peking University International Hospital. The study was designed following the Standard Protocol Items: Recommendations for Interventional Trials (SPIRIT) statement [16] (Fig 1). Participants who meet the inclusion criteria will be randomly assigned at a 1:1 ratio to either the PTC-guided adjuvant chemotherapy group (experimental group) or the traditional chemotherapy group (control group). These participants will then receive different interventions and undergo evaluations throughout the entire duration of the trial (see Fig 2 for a depiction of the study flow). Baseline data will be collected from participants at the beginning of the trial, followed by follow-up assessments at specific intervals. The primary endpoint of the study is the 3-year disease-free survival rate (3yDFS). Through this study, we aim to evaluate the results of PTC drug sensitivity testing in comparison with clinical outcomes, assess the consistency between the results of this technological platform and clinical prognosis, and provide a valuable reference for achieving individualized and precise treatment for CRC patients, thereby improving clinical benefits.

**Fig 1 pone.0326760.g001:**
[figure not shown]
Schedule of enrollment, interventions and assessments.

**Fig 2 pone.0326760.g002:**
[figure not shown]
Flow chart of the study.

### 2.2 Participants and recruitment

We will recruit a total of 200 patients with clinically staged T3-4N0M0 or TanyN + M0 CRC from 9 hospitals in China. The study will document the demographic data, clinical and pathological features, imaging findings, operative results, and oncological outcomes of all enrolled patients.

At this point, we have included all patients clinically staged as T3-4N0M0 or TanyN + M0 in the candidate pool and obtained signed consent forms for the study, but the patients have not yet been enrolled. If patients are determined to require radical resection for CRC after clinical diagnosis and treatment, we will collect approximately 50 mg of fresh cancer tissue with abundant blood vessels from the excised tumor specimens in the operating room after the completion of radical surgery. The samples will be placed in preservation tubes and transported to the laboratory at 4 °C, where PTC model construction will be completed. Upon receipt of the surgical pathology results, if patients indeed meet the criteria for adjuvant chemotherapy, we will select patients on the basis of the inclusion and exclusion criteria.

#### 2.2.1 Inclusion criteria.

The inclusion criteria are as follows: 1) patients with histologically confirmed CRC; 2) baseline clinical stage of cT3-4N0M0 or cTanyN + M0; 3) CRC patients requiring adjuvant treatment after radical surgery and not receiving neoadjuvant treatment; 4) at least one evaluable tumor lesion; and 5) Eastern Cooperative Oncology Group (ECOG) performance status ≤ 2.

#### 2.2.2 Exclusion criteria.

The exclusion criteria are as follows: 1) patients with distant metastases; 2) patients unable to obtain tumor samples; 3) pregnant and lactating women; 4) patients with poor compliance; 5) patients with severe cardiovascular and cerebrovascular complications unable to receive chemotherapy or targeted therapy; 6) patients previously diagnosed with other malignant tumors; 7) patients with severe mental and neurological disorders; and 8) patients deemed unsuitable for participation in this study by researchers.

#### 2.2.3 Participant withdrawal.

Participants have the right to withdraw from the study at any time without providing a reason. Any participants who are lost to follow-up will be recorded, and an intention-to-treat analysis will be performed exclusively for these individuals.

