### 2.4 Intervention

We plan to include 200 patients for analysis, with 100 in the experimental group and 100 in the control group. Both groups will undergo PTC drug sensitivity testing and whole exome sequencing (WES). For the experimental group, doctors will select adjuvant chemotherapy regimens on the basis of the PTC drug sensitivity test results. For the control group, doctors will determine adjuvant chemotherapy strategies on the basis of their clinical experience. The PTC drug sensitivity and WES results will be documented for humanitarian treatment reference after the study concludes or if patients withdraw from the study.

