### 2.5 Therapeutic schemes

#### 2.5.1 PTC drug sensitivity test.

Upon receiving the tumor tissue, the laboratory will verify the sample number and establish a sample file via the laboratory management system for data file management. After laboratory tests are conducted on the sample status (including temperature, time in vitro, and presence of leakage), sample processing and cultivation will be performed. After 2–7 days of cultivation, the formation of PTC clones will be observed via bright field microscopy. If PTC clones fail to form within 7 days, cultivation will be declared unsuccessful, and the patient will be withdrawn. If PTC clones are formed, open field photos will be retained to check for bacterial, fungal, and mycoplasma infections in the culture. Samples identified as negative will be subjected to drug sensitivity experiments [14].

We will test four commonly used adjuvant chemotherapy regimens in clinical practice [19]: fluorouracil+formyltetrahydrofolate (5-RU) [7], oxaliplatin+5-fluorouracil+formyltetrahydrofolate (FOLFOX) [20], irinotecan+5-fluorouracil+formyltetrahydrofolate (FOLFORI) [21,22], and cetuximab+5-fluorouracil+formyltetrahydrofolate [23,24]. For the screening experiment, a 96-well plate will be used, and each experimental group will be equipped with three parallel wells to ensure the reliability of the experimental data. Each sample will be collected twice, once after 0 days of dosing and once after 7 days of dosing. The automatic scanning system will be used to identify the number and area of all PTC clones in the hole. The area ratio of PTC clones (i.e., residual cell viability) after and before dosing will be calculated via the $p_{Ai}=\frac{S_{Ai,t}}{S_{Ai,t0}}$, $p_{A}=\frac{1}{n}\sum_{i=1}^{n}p_{Ai}$ formula [25], and the interpretation criteria are shown in Table 1. The higher the score is, the better the drug’s efficacy in killing tumors, and higher-scoring regimens are more recommended.

**Table 1 pone.0326760.t001:** Criteria for Judging the Drug Sensitivity of PTCs.

Lethality level	Lethality cell percent (%)	Remaining cell percent (%)
**Strong killing effect**	>0.7	0-0.3
**Effective killing effect**	0.3-0.7	0.3-0.7
**Stable**	0.1-0.3	0.7-0.9
**Drug resistant**	0-0.1	0.9-1
**Strongly drug resistant**	0	1

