#### 2.7.3 Statistical methods.

Local recurrence is defined as tumor recurrence in the lumen or in the mesorectum and must be confirmed by a pathological biopsy. A distant metastasis is defined as a metastasis that is discovered in the liver, lung, bone, or other sites by CT, MRI, or radionuclide scanning, with or without pathological examination. Disease-free survival (DFS) is defined as the absence of local recurrence, distant metastasis, and death from any cause. Overall survival (OS) is defined as the absence of death from any cause. The duration of follow-up will be calculated from the date of surgery to the event of interest or the last follow-up date.

To determine the consistency between the PTC drug sensitivity results and clinical outcomes, the following methods will be employed (Table 2): positive consistency rate = a/(a + c) × 100%; negative consistency rate = d/(b + d) × 100%; overall consistency rate = (a + d)/(T1) × 100%; sensitivity = a/(a + b) × 100%; and specificity = d/(b + d) × 100%.

**Table 2 pone.0326760.t002:** Consistency test of recurrence and metastasis cases.

Drug sensitivity test	Clinical efficacy		Sum
	CR + PR	SD + PD	
**Effective**	a	B	a + b
**Invalid**	c	D	c + d
**Sum**	a + c	b + d	T1

The results will be presented as median values or means ± standard deviations for continuous variables and as numbers (percentages) for categorical variables. The t test and Wilcoxon rank sum test will be used to compare continuous variables, and chi-square analysis/Fisher’s exact test will be used to compare categorical variables. Survival analysis will be conducted using the Kaplan-Meier curves. Log-rank test to compare the primary endpoint between different arms in the presence of censoring. A P value of 0.05 or less is considered statistically significant. All the statistical tests will be two-sided. All analyses will be performed using SPSS Version 26.0 (SPSS Inc., Chicago, IL).

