### 2.8 Quality control

To ensure that the quality of research activities meets the requirements, monitoring will be carried out at each stage of data processing to ensure that all the data are trustworthy and processed correctly. The sponsor is responsible for comprehensive tracking and monitoring of the implementation of clinical trials, ensuring that the experiments comply with relevant regulatory requirements and follow the experimental protocol. Clinical trial researchers are familiar with necessary regulatory requirements, possess professional expertise related to clinical trials, have the ability to design and implement relevant clinical trials, are familiar with relevant testing techniques, can correctly interpret test results, have passed qualification review, and are relatively fixed personnel. Laboratory quality control includes establishing unified laboratory standard operating procedures and quality control procedures and conducting quality control simultaneously during drug sensitivity testing. Only when the quality control results are qualified can the data be determined to be valid. The person in charge of statistics has a relevant professional background and abilities.

A double data check will also be performed for quality control. In accordance with the data collection methods and criteria developed by the project leader and professionals, all the data will be recorded carefully and comprehensively to ensure the authenticity of the data. Missing data from withdrawn participants will be imputed via the multiple imputation method.

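### The intention-to-treat sentence is wrong as written, and the plan does not say how censoring and multiple imputation fit together for patients with incomplete DFS follow-up

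*Protocol article*

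**What the plan says.** All references are to the protocol article.

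- **Section 2.2.3 (Participant withdrawal)** says that participants lost to follow-up will be recorded, and then that "an intention-to-treat analysis will be performed exclusively for these individuals". This is the only mention of ITT.
- **Section 2.4 (Intervention)** gives the intended numbers: "We plan to include 200 patients for analysis, with 100 in the experimental group and 100 in the control group". It does not say whether these are randomised patients or patients with usable outcomes.
- **Section 2.7.3 (Statistical methods)** says "The duration of follow-up will be calculated from the date of surgery to the event of interest or the last follow-up date", and for the main comparison "Log-rank test to compare the primary endpoint between different arms in the presence of censoring".
- **Section 2.8 (Quality control)** says "Missing data from withdrawn participants will be imputed via the multiple imputation method". It names no variables.
- **Section 2.5.1 (PTC drug sensitivity test)** adds a withdrawal required by the protocol: "If PTC clones fail to form within 7 days, cultivation will be declared unsuccessful, and the patient will be withdrawn".
- **Section 2.2 (Participants and recruitment)** describes tissue collection and model construction for consented candidates who are not yet enrolled. Selection on the eligibility criteria comes after the pathology result. The article does not say where randomisation falls relative to the culture result.
- **Section 2.7.1 (Sample size)** describes a noninferiority design: 75% three-year DFS, a 20-point margin, two-sided alpha 0.05, 80% power, 74 per group, 20% dropout and 100 per group.

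**The concern.** ITT is a rule for the whole randomised population. Section 2.2.3 applies it only to those lost to follow-up, the group whose outcomes are least complete. A detail left to a separate analysis plan would be no defect. Here the article states a rule and states it wrongly.

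The second issue is how incomplete follow-up enters the primary analysis. Section 2.7.3 points to censoring at the last contact. Section 2.8 points to imputation, without confining it to covariates. An analyst faced with a patient who left at 18 months could censor or impute and cite the article for either. The trial is not double-blind and the planned dropout is 20%, so that choice should be fixed before anyone looks at outcomes by arm.

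Third, section 2.5.1 calls a patient with a failed culture withdrawn. If such a patient has already been randomised, the article does not say whether that patient stays in the comparison.

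**Working it through.** **1. Reproduce the plan's sample size.** Inputs from section 2.7.1: DFS 0.75 (taken as equal in both arms), margin 0.20, one-sided alpha 0.025 (from two-sided 0.05), power 0.80.

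n per arm = (1.96 + 0.842)² × 2 × 0.75 × 0.25 / 0.20² = 7.85 × 0.375 / 0.04 ≈ 73.6, so 74. This matches the stated figure.

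Allowing for 20% dropout: 74 / 0.80 = 92.5, so 93. The planned 100 exceeds this and leaves 100 × 0.80 = 80 per arm.

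**2. Power under the same approximation.** Power = Φ(0.20 / √(0.375/n) − 1.96).

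| n per arm with a 3-year outcome | Power |
|---|---|
| 100 | Φ(3.266 − 1.96) = 90.4% |
| 80 | Φ(2.921 − 1.96) = 83.2% |

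Correcting the analysis set therefore needs no extra patients.

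**3. How much the handling of lost patients can move an arm's result.** Assume that 80 of 100 are observed at 75%, giving 60 disease-free, and that the other 20 are lost before three years. If a proportion q of the lost patients have had an event, the arm's three-year DFS is (60 + 20 × (1 − q)) / 100.

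| q among the 20 lost | Three-year DFS in the arm |
|---|---|
| 0 | 80% |
| 0.25 (same as observed) | 75% |
| 0.50 | 70% |
| 0.75 | 65% |
| 1 | 60% |

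The span is 80 − 60 = 20 points, equal to the noninferiority margin. This is simple counting; it ignores the partial follow-up that censored patients contribute, so the ends are limits.

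**4. Set the sections side by side.** Sections 2.4 and 2.7.3 together imply a comparison between arms of 200 patients. Section 2.2.3 attaches the ITT label to a subset of them. Section 2.7.3 allows for censoring, and section 2.8 imputes for withdrawn participants. The article does not say whether withdrawn and lost to follow-up are the same group, or whether DFS is among the imputed data. Sections 2.2 and 2.5.1 leave open whether a culture failure comes before or after randomisation.

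**The case against.** The best defence is that the ITT sentence is a drafting slip, meant to say that lost patients are kept in the analysis as allocated. Sections 2.4 and 2.7.3 support this. A reader might infer from section 2.2.3 that the randomised comparison would not be analysed at all; the article does not support that, because a between-arm test of the primary endpoint is planned. The sentence is still wrong, and it is the only ITT rule given.

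Several stronger readings also fail.

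- **Censoring and imputation as a contradiction.** Section 2.7.3 never says that withdrawn patients are censored, and section 2.8 never says that DFS is imputed; it may mean covariates. The two are unreconciled, which is a weaker charge.
- **An ITT set of about 20 per arm.** Taken literally, the 95% interval half-width would be 1.96 × √(0.375/20) = 26.8 points, wider than the margin. The arithmetic is right, but nobody would run that analysis, and it treats lost patients as having observed outcomes.
- **Power lost to culture failures.** Failures of 10% to 30% on top of 20% dropout would leave 72 to 56 per arm and power of 79% to 69%. No failure rate is given, and section 2.2 allows failures to occur before enrolment. They might also be part of the 20%.
- **An incentive for control patients to withdraw.** Section 2.4 says that results are "documented for humanitarian treatment reference after the study concludes or if patients withdraw from the study". That shows no pattern of withdrawal by arm.
- **Bias toward noninferiority.** The direction is not determined. If control patients with poor prognosis left, the control arm would look better, which works against noninferiority. No imputation model is described.

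**Conclusion.** The point stands in a limited form. The ITT sentence in section 2.2.3 is wrong and uncorrected, and it bears on the primary comparison. The handling of incomplete DFS in sections 2.7.3 and 2.8, and the status of culture failures in sections 2.2 and 2.5.1, need to be reconciled.

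The size is best expressed by the 60% to 80% range for an arm's three-year DFS. That range assumes that all of the planned 20% dropout falls before three years, that the loss is 20 per arm, and that the observed patients are at 75%. Follow-up runs for five years, so some patients lost late would already have a three-year outcome, and the real range would be narrower. The documents do not show that the trial is underpowered, that withdrawal differs by arm, or that the result would be biased in a particular direction.

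**What to change.** 1. Replace the sentence in section 2.2.3 with: *The primary analysis includes all randomised patients in the arm allocated (ITT); a per-protocol analysis is supportive for the noninferiority conclusion.*
2. In section 2.7.3, state that patients with incomplete DFS follow-up are censored at their last disease assessment in the primary analysis.
3. In section 2.8, state that multiple imputation does not replace the DFS outcome in the primary analysis, and name what it does cover. Add one sensitivity analysis for lost patients that varies the assumption about their outcomes.
4. Reconcile sections 2.2 and 2.5.1: say that a culture failure before randomisation is a screen failure, and that any patient already randomised stays in the ITT set with DFS follow-up continued.

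The cost is an amendment to the wording and one added sensitivity analysis. No change in sample size is needed.
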